#### 2.9.3 Statistical Analysis

Baseline characteristics, procedural data, and follow-up outcomes will be 
summarized using descriptive statistics. Continuous variables will be presented 
as means ± standard deviations (SD) if normally distributed, or as medians 
with interquartile ranges (IQR) if non-normally distributed. Categorical 
variables will be expressed as frequencies and percentages.

The primary efficacy analysis will be conducted in the ITT population using a 
one-sample proportion Z-test to evaluate whether the proportion of patients 
achieving MR ≤1+ at 12 months exceeds the prespecified OPG of 75%. A 
one-sided significance level of 0.025 will be applied to test the null hypothesis 
that the success rate is less than or equal to the OPG.

Secondary endpoints will be analyzed descriptively. Comparisons of continuous 
variables between baseline and follow-up will use paired *t*-tests or 
Wilcoxon signed-rank tests based on data distribution. Categorical variables will 
be compared using McNemar’s test or Cochran’s Q test, as appropriate. 
Time-to-event outcomes will be analyzed using Kaplan–Meier estimates, with 
median survival times and event-free rates calculated at 30 days, 6 months, and 
12 months. Log-rank tests may be applied for subgroup comparisons where relevant.

To assess long-term durability, all subjects will be followed for up to five 
years. A secondary Bayesian analysis will be performed to estimate the posterior 
probability of sustained therapeutic success (defined as MR ≤1+ without 
mitral valve replacement or reintervention). This approach enables dynamic 
updating of treatment effect estimates over time and offers further insight into 
outcomes beyond the 12-month endpoint.

Predefined subgroup analyses will be performed according to the three 
morphological subtypes to evaluate the efficacy and safety of the 
classification-guided M-TEER strategy. Due to distinct procedural approaches and 
expected small sample sizes within subgroups, a dual analytic strategy will be 
employed: exact tests will be used for small-sample inference, while Bayesian 
methods will provide probabilistic estimations with credible intervals, 
incorporating prior knowledge to enhance robustness.

Sensitivity analyses will be conducted to evaluate the stability of the primary 
outcome results. These will include analyses based on the PP 
population—excluding major protocol deviations—and scenario-based imputations 
for missing data (e.g., worst-case and best-case assumptions). Consistency 
between the ITT and PP populations, as well as across imputation methods, will 
strengthen the reliability of trial conclusions.

All statistical analyses will be conducted using a one-sided alpha level of 
0.025. Analyses will be performed using SAS software (version 9.4; SAS Institute 
Inc., Cary, NC, USA), R software (version 4.2.1; R Foundation for Statistical 
Computing, Vienna, Austria), and SPSS software (version 24.0; IBM Corp., Armonk, 
NY, USA).

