### 2.9 Statistical Considerations

#### 2.9.1 Sample Size Calculation

The primary endpoint of this study is the proportion of patients achieving a MR 
grade of ≤1+ without repeat mitral intervention at 1-year follow-up. The 
study is designed as a single-arm, objective performance goal (OPG) trial with 
the following statistical hypotheses:

*H₀: P_𝑇_
≤ P₀*

*H₁: P_𝑇_
> P₀*

where *P*_𝑇_ represents the expected primary endpoint rate in this 
study, and *P₀* denotes the target performance level derived from previous 
literature.

Based on our center’s retrospective data and relevant published studies [16], 
the expected rate of the primary endpoint (*P*_𝑇_) was set at 85%. The 
target performance level (*P₀*) was set at 75%, reflecting clinically 
acceptable outcomes reported for complex MR populations in previous trials [17].

Using a one-sided significance level (α) of 0.025, a statistical power 
(1–β) of 80%, and assuming a 10% dropout rate at 12-month follow-up, 
the required sample size was calculated to be 148 patients. The sample size 
calculation was performed using the formula for a one-sample proportion test 
against a performance goal:

$$n=\frac{{\left[Z_{1-\alpha }\cdot \sqrt{P_{0}\,\left(1-P_{0}\right)}+Z_{1-\beta }\cdot \sqrt{P_{T}\,\left(1-P_{T}\right)}\right]}^{2}}{{\left(P_{T}-P_{0}\right)}^{2}}$$

where *Z*_1-α_ = 1.96 for a onesided α of 0.025, and 
*Z*_1-β_ = 0.84 for 80% power. 

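### At the planned 10% dropout, agreement between worst-case and best-case imputation can rarely support a result that performs as designed, so it is a poor sign of reliability

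*Protocol article*

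**What the plan says.** Section 2.9.3 plans sensitivity analyses to examine how stable the primary result is. One is the per-protocol analysis. The other is scenario-based imputation "for missing data (e.g., worst-case and best-case assumptions"). The section then states how the results are to be taken: consistency between the ITT and PP populations, and "across imputation methods, will strengthen the reliability of trial conclusions". No other scenario is named, and nothing is said about how disagreement would be read.

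The primary analysis is a "one-sample proportion Z-test to evaluate whether the proportion of patients" with MR ≤1+ at 12 months exceeds the goal, and a "one-sided significance level of 0.025 will be applied to test the null hypothesis". Section 2.9.1 supplies the design values. The goal "was set at 75%, reflecting clinically" acceptable outcomes, the expected rate is 85%, and "the required sample size was calculated to be 148 patients", "assuming a 10% dropout rate at 12-month follow-up".

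**The concern.** Worst-case imputation counts every missing patient as a failure, and best-case counts every one as a success. The distance between the two imputed rates is therefore the missing fraction, whatever is observed. Here the planned missing fraction is 10% and the margin that the trial is built to detect is also 10 points. A trial that performs as planned should then usually pass under one bound and fail under the other.

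This matters for interpretation. A sponsor with a genuine success would usually be unable to claim the consistency that the plan treats as supporting evidence. A reader would learn little about whether the positive result is fragile or secure, because a wide range of observed results gives the same split between the bounds.

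**Working it through.** **Inputs.** From section 2.9.1: P0 = 0.75, P_T = 0.85, one-sided alpha 0.025, power 80%, dropout 10%, N = 148. From section 2.9.3: one-sample Z-test of a proportion against 75%.

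**1. The plan's own sample size.** n = [z(0.975)·√(0.75×0.25) + z(0.80)·√(0.85×0.15)]² / 0.10². With full-precision normal quantiles this is 132.07, rounded up to 133. Then 133/0.90 = 147.8, rounded up to 148, which reproduces the stated figure. (The rounded multipliers printed in the article, 1.96 and "0.84 for 80% power", give 131.9, a difference that does not matter here.) So the plan expects 133 observed and 15 missing.

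**2. Pass mark with all 148 in the denominator.** The standard error under the null is √(0.1875/148) = 0.0356. The rate needed is 0.75 + 1.96×0.0356 = 0.820, or 121.3 patients, so the test passes at 122/148 (82.4%). The exact binomial test has the same pass mark.

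**3. Width of the bounds.** 15/148 = 10.1 points. At a true rate of 85%, the expected imputed rates at 10% missing are 0.90×0.85 = 76.5% (worst case) and 76.5% + 10% = 86.5% (best case). The pass mark of 82.4% lies between them.

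**4. Verdicts with 15 missing.** Let X be the successes among the 133 observed, X ~ Binomial(133, p), with missingness independent of outcome. Worst case passes if X ≥ 122, an observed rate of 122/133 = 91.7%. Best case passes if X + 15 ≥ 122, so X ≥ 107. The verdicts disagree when 107 ≤ X ≤ 121.

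| True rate | Worst case passes | Best case passes | Verdicts disagree |
|---|---|---|---|
| 75% | 0.0% | 8.6% | 8.6% |
| 80% | 0.02% | 50.0% | 50.0% |
| 85% | 1.5% | 94.0% | 92.5% |
| 90% | 31.2% | 99.97% | 68.8% |

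At a true rate of 93%, worst case passes 78% of the time.

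**5. Comparison with the observed-case test.** On 133 patients that test needs 110 successes and passes 80.8% of the time at 85%. Worst case also passes in 1.5/80.8, about 1.9%, of those trials.

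**6. Varying the number missing, at a true rate of 85%.**

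| Missing | Verdicts disagree |
|---|---|
| 16 | 93.7% |
| 15 | 92.5% |
| 14 | 90.8% |
| 10 | 75.5% |
| 7 | 53.7% |
| 5 | 36.4% |

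If dropout is itself random at 10%, the figure is 88.6%. With 15 missing and the Wald variance it is 93.3%.

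**7. What the split between the bounds hides.** Three positive results with 133 observed and 15 missing all give the same pair of verdicts: best case passes, worst case fails. They differ in how many of the 15 missing patients must have succeeded for the total to reach 122.

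| Observed successes | Successes needed among the missing |
|---|---|
| 110/133 (82.7%) | 12/15 (80%) |
| 113/133 (85.0%) | 9/15 (60%) |
| 118/133 (88.7%) | 4/15 (27%) |

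The first result is fragile and the third is fairly secure. A tipping point shows the difference; the pair of verdicts does not.

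**The case against.** The strongest reply is that the article contains no agreement rule. Its sentence works in one direction: consistency adds confidence. It gives no consequence for disagreement and does not define consistency as matching test verdicts. ITT–PP agreement is listed as well. This stands, and a reader who infers a formal pass/fail criterion goes beyond the text.

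Second, the scenarios are introduced as examples, and an analysis plan that is not shown may add others. This also stands, so the absence of further methods is not held against the article. It does not remove the point, however. While these two scenarios are among those compared, their disagreement is enough to break consistency across methods.

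Third, worst-case and best-case imputation are legitimate outer bounds, and a width equal to the missing fraction is how they work. Showing that missing data could overturn the result is honest information. Agreed; the weakness lies only in treating agreement between them as a mark of reliability.

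Fourth, a reader might infer that the comparison is settled by dropout alone and carries no information about the data. The numbers do not support that. With 15 missing, the worst case passes 1.5% of the time at a true 85%, 31% at 90% and 78% at 93%, so it does separate very strong results from ordinary ones, though strictly. Both bounds failing at a true 75% is correct behaviour.

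Finally, the best-case pass rate of 8.6% at a true 75% might be read as an inflated error rate for the trial. It is not, because nothing in the article uses the best case alone as confirmation.

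**Conclusion.** The point holds as a weakness in how the named sensitivity scenarios are to be interpreted. At the protocol's own dropout and effect assumptions, the bounds are about as far apart as the goal and the expected rate. Read as matching one-sided 0.025 verdicts, they disagree in about 92% of trials that perform as designed.

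That figure rests on three assumptions: 15 of 148 missing, missingness unrelated to outcome, and that reading of consistency. Realised dropout is unknown, and the problem shrinks quickly if follow-up is better than planned. The primary test, its alpha and the sample size are untouched. Severity is minor to moderate.

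**What to change.** In section 2.9.3:

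- Keep worst-case and best-case imputation as descriptive outer bounds, and do not use agreement between them as the sign of reliability.
- Add a tipping-point analysis. Report the success rate among patients with missing 12-month status at which the one-sided 0.025 conclusion is lost, and set it beside the rate in those observed.
- Support it with multiple imputation of 12-month MR status from baseline, 30-day and 6-month MR grade and morphological type.

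No new data are needed. Section 2.6.3 already schedules echocardiography at baseline, 30 days and 6 months, and section 2.2 has the core laboratory grade MR at baseline and follow-up. The cost is a few sentences of text and slightly more programming. The downside is that a tipping point calls for a judgement of plausibility and does not give a yes or no.

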## 3. Discussion

The TEER-CD trial represents a significant advancement in the field of 
interventional cardiology, addressing a critical gap in the management of 
commissural DMR. Utilizing a prospective, multicenter, single-arm, OPG design, 
the study adopts a refined TEER approach tailored to the unique anatomical 
challenges of commissural DMR. The implications of this research are 
far-reaching, as it could lead to a paradigm shift in the management of 
commissural DMR. With an aging global population and an increasing prevalence of 
valvular heart disease, the need for effective and less invasive treatment 
options is more critical than ever. The TEER-CD study is poised to make a 
significant contribution to the field, offering hope to patients who have 
historically been underserved by existing therapies.

### 3.1 Innovative Morphological Classification System

The introduction of a detailed morphological classification system is a 
cornerstone of this trial. By categorizing patients into distinct subtypes based 
on their echocardiographic features, the study allows for a personalized 
treatment strategy, optimizing the procedural approach for each patient’s unique 
valve morphology. This systematic categorization is expected to enhance 
procedural precision and outcomes, potentially reducing complications and 
improving repair efficacy.

### 3.2 Clinical Implications and Potential Impact

The implications of the TEER-CD trial are profound, promising to expand the 
applicability of M-TEER to a patient population that has historically been 
underserved by traditional methods. The study’s focus on commissural DMR is 
particularly noteworthy, given that this subset of patients often presents with 
more advanced disease at diagnosis and has been frequently excluded from clinical 
trials. The potential for this study to refine treatment guidelines and broaden 
the therapeutic scope of M-TEER is substantial.

### 3.3 Methodological Considerations

The use of an OPG design allows for targeted evaluation of the efficacy of the 
novel morphology classification-guided M-TEER strategy in patients with 
commissural DMR. This design is appropriate in the absence of an established 
comparator group for this anatomical subset. The total sample size of 148 
patients is sufficient to support the primary efficacy objective and allows for 
descriptive and exploratory analyses of secondary endpoints. A planned 5-year 
follow-up, supplemented by a secondary Bayesian analysis at extended time points, 
will provide insights into the long-term durability of treatment effects beyond 
the 12-month primary analysis. To evaluate treatment effects across different 
anatomical subtypes, pre-specified subgroup analyses will be conducted. Given the 
relatively small sample sizes in each subgroup, the use of exact tests and 
Bayesian methods enhances the analytical robustness by enabling reliable 
inference without strict distributional assumptions and by incorporating prior 
information to refine estimates.

### 3.4 Limitations and Future Research

While the TEER-CD trial is methodologically robust, it is not without 
limitations. The single-arm design, though appropriate for this innovative 
intervention, limits the ability to make direct comparisons with other 
treatments. Future research should consider randomized controlled trials to 
directly compare the novel morphological classification-guided M-TEER with 
existing therapies.

Additionally, the generalizability of the study’s findings may be limited by the 
demographic and geographic diversity of the study population. Future studies 
should aim to include a more diverse patient population to enhance the global 
applicability of the results.

## 4. Conclusions

In summary, the TEER-CD trial is poised to make a significant contribution to 
the field of structural heart disease, particularly in the treatment of 
commissural DMR. By introducing a novel classification system and personalized 
procedural strategies, this study has the potential to transform clinical 
practice, offering new hope to patients with this complex and challenging 
condition. As the field of interventional cardiology continues to evolve, studies 
like TEER-CD are essential for driving innovation and improving patient outcomes.

## Data Availability

No datasets were generated or analyzed during the current study.

## Abbreviations

2D, two-dimensional; 3D, three-dimensional; AC, anterolateral commissure; ACC, 
American College of Cardiology; AHA, American Heart Association; Ant, anterior; 
AV, aortic valve; AVP, Amplatzer Vascular Plug; CABG, coronary artery bypass 
grafting; CD, commissural disease; DMR, degenerative mitral regurgitation; ECL, 
echocardiographic core laboratory; ESC, European Society of Cardiology; FMR, 
functional mitral regurgitation; HF, heart failure; IBM, International Business 
Machines Corporation; I/E, inclusion and exclusion criteria; IQR, interquartile 
range; ITT, intention-to-treat; KCCQ, Kansas City Cardiomyopathy Questionnaire; 
Lat, lateral; LAX, long-axis; LVAD, left ventricular assist device; LVEDV, left 
ventricular end-diastolic volume; LVESD, left ventricular end-systolic diameter; 
M-TEER, mitral transcatheter edge-to-edge repair; MC, mitral commissure; ME, 
mid-esophageal; Med, medial; MR, mitral regurgitation; MV, mitral valve; MVARC, 
Mitral Valve Academic Research Consortium; NYHA, New York Heart Association; OPG, 
objective performance goal; PASP, pulmonary artery systolic pressure; PC, 
posteromedial commissure; PCI, percutaneous coronary intervention; Post, 
posterior; PP, per-protocol; PVR, pulmonary vascular resistance; SAS, Statistical 
Analysis System; SAX, short-axis; SD, standard deviation; SLDA, single leaflet 
device attachment; SPSS, Statistical Package for the Social Sciences; TAPSE, 
tricuspid annular plane systolic excursion; TAVR, transcatheter aortic valve 
replacement; TEE, transesophageal echocardiography; TEER, transcatheter 
edge-to-edge repair; TTE, transthoracic echocardiography; USA, United States of 
America.
